**5.2. Drugs: storage and administration**

Isoniazid/pyridoxine hydrochloride (Cemidon®), rifampicin (Rifaldin® or Rimactán®), and rifapentine (Priftin®), will be stored in a cool, dry place. Each batch of tablets will be labelled in the Pharmacy Department and then transported to the outpatient clinic where participants will be attended to. PI in each centre will record the batch number and its expiration date, to warrant sample traceability as RD 1090/2015 establishes, with the rest of data required.

**5.3. Medications permitted and not permitted during the trial**

- **Medications not permitted with isoniazid.** The following medications must not be given concomitantly with isoniazid: carbamazepine and disulfiram. Although, according to the datasheet of the Agencia Española del Medicamento y Productos Sanitarios (AEMPS) *(attachment 1a)*, these are relative contraindications, for the purpose of the study, these two drugs will not be permitted concomitantly with isoniazid.
- **Medications not permitted with rifampicin.** The following medications must not be given concomitantly with rifampicin, as they are contraindicated in the datasheet of the drug, because of major interaction *(attachments 1b & 1c)*: antiretrovirals (saquinavir/ritonavir o elvitegravir/cobicistat, atazanavir, darunavir, fosamprenavir, tipranavir, rilpivirine o dolutegravir/rilpivirine), antihypertensive drugs (nifedipine, nimodipine, nisoldipine o nitrendipine), protease inhibitors anti-C virus hepatitis (glecaprevir/pibrentasvir o elbasvir/grazoprevir), antifungal drugs (ketoconazole, itraconazole y voriconazole), immunosuppressors (cyclosporin, tacrolimus), antimalarials (artemether/lumefantrine).

For other medications with significant interaction with rifampicin, they can be given if under the investigator’s judgement, with dose adjustment and close monitoring of the potential derived adverse events, the benefits outweigh the potential harms.

- **Medications not permitted with rifapentine.** Medications with significant interaction with rifapentine can be given if under the investigator’s judgement, with dose adjustment and close monitoring of the potential derived adverse events, the benefits outweigh the potential harms *(attachment 1d)*.

**5.4. Discontinuation of study drugs due to adverse events**

Certain events or conditions may necessitate temporary discontinuation of the study medications. Patients who experience such events or conditions, however, will still be "on study" and will be followed until study completion. Any patient for whom the study medication is temporarily discontinued will be restarted on study medication as soon as possible. If study drugs are definitively discontinued, alternative therapy for latent TB may be administered at the investigator's discretion.

- **Temporary Discontinuation**

Criteria for temporary discontinuation of the study medication:

- Development of a toxicity that, depending on its nature and severity, requires discontinuation of the study medication until the toxicity resolves as indicated in the preceding toxicity management section.
- Development of another medical condition that makes the administration of the study drug inadvisable. The decision to temporarily discontinue the study medication in this situation will be at the investigator's discretion. The period during which the patient is off study medication will be as short as clinically possible.
- **Definitive Discontinuation**

Criteria for definitive discontinuation of study therapy:

- Development of a toxicity that warrants definitive discontinuation of any study medications.
- The patient refuses further study therapy. If a patient refuses further study medication, they will be treated with a non-study regimen, and there will only be a post-treatment visit, four weeks after discontinuing the treatment.
- In the investigator's judgment, continuation of the medication is no longer in the best interest of the patient.
- Liver toxicity: ALT and/or AST elevation >5-fold of the upper limit of the normality or clinical hepatitis during treatment for latent TB infection with one of the IMPs.
- Neurotoxicity: Encephalopathy, dizziness, or cerebellar syndrome during treatment with INH-including regimens. It is commonly referred to as feeling “drunk”. It is usually invalidating and improved after discontinuing treatment.

**6. ASSESSMENT OF EFFICACY**

**6.1. Efficacy parameters**

The outcome to assess efficacy will be completion of the assigned treatment.

**6.2. Methods and timing for assessment**

Assessment of treatment completion will be done at the end of the maximum pre-specified time frame in which the treatment should be completed (see **section 3.1. “Statement of the endpoints”** for definition of treatment completion). The time frame will be different for each of the three study arms: 16 weeks since the date of the first treatment dose, for the 3HR arm (control); 14 weeks since the date of the first treatment dose, for the 3HP arm (experimental 1), and 20 weeks since the date of treatment dose, for 4R arm (experimental 2).

**7. ASSESSMENT OF SAFETY**

**7.1. Monitoring, recording, and reporting of adverse events**

**Adverse event (AE)** is any noxious, unintended, or untoward medical occurrence that may appear or worsen in a subject during the study. It may be a new intercurrent illness, a worsening concomitant illness, an injury, or any concomitant impairment of the subject’s health, including laboratory test values, regardless of aetiology. Any worsening (i.e., any clinically significant adverse change in the frequency or intensity of a pre-existing condition) should be considered an AE.

Any sequel of an accidental or intentional overdose of an investigational product should be reported as an AE or serious adverse event (SAE). In the event of overdose, the subject should be monitored as appropriate and should receive supportive measures as necessary. All subjects will be monitored for AEs during the study.

**All AEs** will be recorded by the investigator from the date the subject gives the written consent to four weeks after finishing the assigned treatment, as well as those serious adverse events made known to the Investigator at any time thereafter that are suspected of being related to one of the Investigational Medical Products (IMPs).

**All AEs** and **SAEs** will be recorded on the AE page of the CRF and in the subject’s source documents.

**7.2. Reference safety information**

In this study the reference safety information (RSI) will be the Summaries of Products Characteristics of IMPs:

- Isoniazid/pyridoxine hydrochloride (Cemidon®)
- Rifampicin (Rifaldin® or Rimactán®)
- Rifapentine (Priftin®)

**7.3. Evaluation of adverse events**

A qualified Investigator will evaluate all adverse events as to:

- **Seriousness**
- **Serious adverse event.** A SAE is any AE occurring at any dose that:
- Results in death
  - Is life-threatening (i.e., in the opinion of the Investigator, the subject is at immediate risk of death from the AE)
  - Requires participant inpatient hospitalization or prolongation of existing hospitalization (hospitalization is defined as an inpatient admission, regardless of length of stay)
  - Results in persistent or significant disability/incapacity (a substantial disruption of the subject’s ability to conduct normal life functions)
  - Results in a congenital anomaly/birth defect
  - Important medical events are defined as those occurrences that may not be immediately life threatening or result in death, hospitalization, or disability, but may jeopardize the subject or require medical or surgical intervention to prevent one of the other outcomes listed above
  - **Events not considered to be SAEs are hospitalizations for:**
- A standard procedure for protocol therapy administration. However, hospitalization or prolonged hospitalization for a complication of therapy administration will be reported as an SAE.
- Routine treatment or monitoring of the studied indication not associated with any deterioration in condition
- The administration of blood or platelet transfusion as routine treatment of studied indication. However, hospitalization or prolonged hospitalization for a complication of such transfusion remains a reportable SAE.
- A procedure for protocol/disease-related investigations (e.g., surgery, scans, endoscopy, sampling for laboratory tests, bone marrow sampling). However, hospitalization or prolonged hospitalization for a complication of such procedures remains a reportable SAE.
- Hospitalization or prolongation of hospitalization for technical, practical, or social reasons, in absence of an AE
- A procedure that is planned (i.e., planned prior to starting of treatment on study); must be documented in the source document and the CRF. Hospitalization or prolonged hospitalization for a complication remains a reportable SAE.
- An elective treatment of a pre-existing condition unrelated to the studied indication
- Emergency outpatient treatment or observation that does not result in admission, unless fulfilling other seriousness criteria above
- If an AE is considered serious, both the AE page of the CRF and the SAE Report Form must be completed. For each AE/SAE, the Investigator will provide information on severity, and start and stop dates, relationship to IMP, action taken regarding IMP, and outcome.
- **Casualty**

The Investigator must determine the relationship between the administration of IMP and the occurrence of an AE/SAE as Not Suspected or Suspected as defined below:

**Not related**: A causal relationship of the adverse event to IMP administration is unlikely or remote, or other medications, therapeutic interventions, or underlying conditions provide a sufficient explanation for the observed event.

**Related:** There is a reasonable possibility that the administration of IMP caused the adverse event. ‘Reasonable possibility’ means there is evidence to suggest a causal relationship between the IMP and the adverse event.

Causality should be assessed and provided for every AE/SAE based on currently available information. Causality is to be reassessed and provided as additional information becomes available.

- **Unexpectedness**

An unexpected adverse reaction (UAR) is defined as any adverse reaction whose nature or severity is not consistent with the reference safety information (RSI).

A **suspected unexpected serious adverse reaction (SUSAR)** is an adverse reaction that is both serious and unexpected.

- **Duration**

For both AEs and SAEs, the Investigator will provide a record of the start and stop dates of the event.

- **Action taken with IMP and/or adverse event**

The Investigator will report the action taken with IMP because of an AE or SAE, as applicable (e.g., discontinuation or reduction of IMP, as appropriate) and report if concomitant and/or additional treatments were given for the event.

- **Outcome**

The investigator will report the outcome of the event for both AEs and SAEs.

All SAEs that have not been resolved upon discontinuation of the subject’s participation in the study must be followed until recovered, recovered with sequelae, not recovered (death due to another cause) or death (due to the SAE).

**7.4. Abnormal laboratory values**

An abnormal laboratory value is an AE if the abnormality: results in discontinuation from the study; requires treatment, modification/interruption of IMP dose, or any other therapeutic intervention; or is judged to be of significant clinical importance.

Regardless of severity grade, only laboratory abnormalities that fulfill a seriousness criterion need to be documented as a serious adverse event.

If a laboratory abnormality is one component of a diagnosis or syndrome, then only the diagnosis or syndrome should be recorded on the AE page of the CRF. If the abnormality was not a part of a diagnosis or syndrome, then the laboratory abnormality should be recorded as the AE. If possible, the laboratory abnormality should be recorded as a medical term and not simply as an abnormal laboratory result (eg, record thrombocytopenia rather than decreased platelets).

**7.5. Pregnancy**

The Investigator should report all pregnancies in female clinical trial subjects or study subject’s partner to UICEC-IDIBELL within 24 hours of becoming aware of the information, using the UICEC-IDIBELL Pregnancy Notification Form.

- **Female of childbearing potential**

Pregnancies and suspected pregnancies (including elevated βhCG or positive pregnancy test in a female subject of childbearing potential regardless of age or disease state) occurring while the subject is on IMP, or within the time considered in the RSI of the subject’s last dose of IMP, are considered immediately reportable events. If the IMP is rifapentine, it must be discontinued immediately. The pregnancy/ suspected pregnancy must be reported to UICEC-IDIBELL by email and by sending a completed Pregnancy Notification Form. The female subject may be referred to an obstetrician-gynaecologist or another appropriate healthcare professional for further evaluation

The Investigator will follow the female subject until completion of the pregnancy, and must notify UICEC-IDIBELL immediately about the outcome (either normal or abnormal outcome) of the pregnancy (including spontaneous abortion or voluntary termination, details of birth and the presence or absence of any birth defects, congenital abnormalities or maternal and new-born complications) by email, and by sending a completed Pregnancy Notification Form.

If the outcome of the pregnancy was abnormal (e.g., spontaneous, or therapeutic abortion), the Investigator should report the abnormal outcome as an AE. If the abnormal outcome meets any of the serious criteria, it must be reported as an SAE to UICEC within 24 hours of the Investigator’s knowledge of the event using the SAE Notification Form.

All neonatal deaths that occur within 28 days of birth should be reported, without regard to causality, as SAEs. In addition, any infant death within 28 days that the Investigator suspects is related to the in-utero exposure to the IMP should also be reported to UICEC-IDIBELL as an SAE within 24 hours of the Investigator’s knowledge of the event using the SAE Notification Form. To ensure that the investigator will perform the follow-up, if UICEC-IDIBELL has not received the follow-up information, UICEC-IDIBELL will contact the investigator two (2) weeks after expected delivery date for this accomplishment. Every infant must be followed for 28 days after delivery (if applicable).

- **Male subjects**

If a female partner of a male subject taking investigational product becomes pregnant, the male subject taking IMP should notify the Investigator, and the pregnant female partner should be advised to call their healthcare provider immediately.

If a pregnancy related event is reported in a female partner of a male subject, the investigator should ask if the female partner is willing to share information with UICEC-IDIBELL and allow the pregnancy related event to be followed up to completion.

**7.6. Reporting of serious adverse events**

All **SAEs** (initial and follow up information) must be reported to UICEC-IDIBELL within 24 hours of the Investigator’s knowledge of the event by email, using the SAE Report Form and the contact information provided in the protocol. This requirement applies to all SAEs, regardless of relationship to IMP that occur during the study or any SAEs made known to the Investigator at any time thereafter that are suspected of being related to IMP.

The SAE report should provide a detailed description of the SAE and include a concise summary of hospital records with relevant items or other relevant documents. If a subject died and an autopsy has been performed, copies of the autopsy report and death certificate are to be sent to UICEC-IDIBELL if available. UICEC-IDIBELL will confirm that the notification is valid within days by e-mail. If the notification is not valid, UICEC-IDIBELL will request the information to the researcher via email.

**7.7. Procedure for expedited reporting of serious unexpected adverse reactions**

If an adverse event report meets the following three criteria, then the event is reportable in an expedited manner to all concerned Regulatory Authorities, concerned ethical committee and to all participating investigators:

- Serious
- Unexpected
- Associated with the use of some Investigational Medicinal Products.

All relevant information about suspected serious unexpected adverse reactions that are fatal or life-threatening is reported as soon as possible and, in any case, no later than seven calendar days after the investigator is aware of by UICEC-IDIBELL of such a case, and that relevant follow-up information is subsequently communicated within an additional eight calendar days.

All other SUSARs will be reported as soon as possible but within a maximum of 15 calendar days of knowledge. The Sponsor will notify regulatory authorities, as soon as possible and no later than 15 days after having knowledge of it, any information that could alter the benefit/risk relationship of the investigational medicinal product (e.g. an increase in the rate of occurrence of the expected SAR, SUSARs that occur after the completion of a clinical trial, new events related to the conduct of the trial or the development of the investigational medicinal product, any recommendation of the Data Monitoring Committee where relevant for the safety of subjects, etc.).

**7.8. Special interest adverse events**

- Liver toxicity
- Neurotoxicity
- Hypersensitivity

These events will be reported as a SAE, they will be considered an “Important Medical Event” even if no other serious criteria apply.

**7.9. Annual safety report**

During the study, the sponsor or a delegated unit by the sponsor will prepare periodic safety reports annually following the recommendations outlined in the ICH E2F guidelines, and they must be submitted to the regulatory authorities and the ECs involved following the timetable established in the legislation.

**7.10. Report to the investigators**

The sponsor shall present the safety information that could affect the safety of the participants included in the study to the investigators as soon as possible.

The SUSAR information will be sent annually through a line listing, together with a summary of the data analysis. In addition, the investigator will be informed throughout the study about all safety aspects, including amendments to the protocol due to safety reasons.

**7.11. Data and safety monitoring board** **(DSMB)**

The DSMB will meet once the first 110 participants have been recruited, and there are at least 6 months of follow-up for the last participant is included.

The membership, and the study aspects to be reviewed, will be specified in the DSMB Charter. The DSMB chairperson will be responsible for providing a written report of findings and recommendations to the sponsor in a timely manner. The sponsor will be responsible for informing the study sites and appropriate regulatory authorities of any DSMB recommendation relating to conduct of the study.

**8. STATISTICAL METHODS**

**8.1. Statistical analysis**

The efficacy analysis will be performed on the modified intention-to-treat population, which will consist of all randomized subjects. The proportions of participants who completed the assigned treatment in the 3HR arm (control) will be compared with the proportions in either 3HP arm (experimental 1) or 4R arm (experimental 2). Since renal replacement therapy could have a potential influence on medication tolerance, especially INH, and thus could influence outcome, the analysis for the primary endpoint will be performed for the population as a whole and by subgroups (non-dialysis, on haemodialysis, or on peritoneal dialysis).

For safety, analyses will be performed on all randomized subjects who have received at least one dose of the assigned study treatment. Likewise, proportions of permanent discontinuation of the assigned treatment, related and unrelated to the study medication, and death, in the control arm will be compared with either experimental arm.

Statistical analyses will be performed by two investigators of the Biostatistics Unit of the IDIBELL, who will remain unaware of the trial-group assignments until the analyses have been completed. Differences between arms will be tested by Student’s t-test, if normally distributed, or a Wilcoxon two-sample test, if not normally distributed, or by chi-square analysis for categorical variables. Whenever possible, estimators will be given 95%CI. Statistical significance was set at a p-value <0.025. Treatment of the data and analysis will be performed with the statistical package R, version 3.4.1 or superior.

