**4.3. Participant withdrawal criteria**

Each participant has the right to withdraw study at any time. In addition, the investigator may discontinue a participant from the study at any time if they consider it necessary for any reason including:

- An adverse event that requires discontinuation of the study medication, mainly liver toxicity caused by isoniazid or rifamycins.
- Non-attendance at two consecutive visits, if it was not because of death.
- Not completing the assigned treatment, for any reason, within the scheduled frame-time (1. not completion of 90 doses within a maximum of 16 weeks, without interruptions longer than 2 weeks, and no more than on 2 occasions, for the 3HR arm [control]; 2. not completing 12 doses within a maximum of 14 weeks, without interruptions longer than 10 days, for the 3HP arm [experimental 1] , and 3. Not completion of 120 doses within a maximum of 20 weeks, without interruptions longer than 2 weeks, and no more than on two occasions, for the 4R arm [experimental arm 2]).

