**8.2. Sample size**

The sample size has been calculated to demonstrate a clinically significant better completion with the 3HP or 4R regimens than the 3HR regimen. With an α= 0.025, β= 0.20, and 5% expected losses, and assuming a 0.75 proportion of treatment completion in the control arm (3HR), according to our previous experience, 225 subjects (75 per arm) will be needed to demonstrate, if exists, a 0.16 increase in treatment completion rates in the experimental arms (4R or 3HP) respectively. Sample size was calculated with GIGAcalculator (<https://www.gigacalculator.com/calculators/power-sample-size-calculator.php>).

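### The efficacy set is labelled modified ITT but defined as all randomised, the 5% loss allowance does not fit it, and 75 per arm does not give the stated 80% power on that set

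*Protocol*

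**What the plan says.** Protocol section 8.1 defines the efficacy set: "The efficacy analysis will be performed on the modified intention-to-treat population, which will consist of all randomized subjects". The only restricted set in that section is for safety, where "analyses will be performed on all randomized subjects who have received at least one dose of the assigned study treatment".

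Section 8.2 gives the planning inputs: "With an α= 0.025, β= 0.20, and 5% expected losses", "assuming a 0.75 proportion of treatment completion in the control arm (3HR), according to our previous experience", and "a 0.16 increase in treatment completion rates in the experimental arms (4R or 3HP) respectively". From these it concludes that "225 subjects (75 per arm) will be needed to demonstrate" the effect. It does not define losses, say how the 5% enters the calculation, say whether 0.75 and 0.91 include losses, or say whether 0.025 is one- or two-sided.

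Section 3.1 defines completion as 90, 12 or 120 doses within 16, 14 or 20 weeks, with limits on interruptions. Section 6.2 places the assessment at the end of that window. Among the grounds for withdrawal, section 4.3 lists "Non-attendance at two consecutive visits, if it was not because of death", and also failure to complete within the window.

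**The concern.** A modified intention-to-treat set normally leaves someone out. Section 8.1 uses the name and then leaves nobody out, so the label and the definition disagree. An allowance for losses normally replaces participants who give no analysable outcome. With a binary completion endpoint and all randomised participants analysed, nobody is missing from the denominator. A person lost before completion is documented has not met the definition in section 3.1 and counts as a failure.

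Two things are at stake. First, losses counted as failures lower both completion rates and shrink the difference between them. A small increase in sample size does not make up for this. Second, section 8.2 states a power, and that power should be the one the section 8.1 analysis delivers.

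**Working it through.** **Inputs.** From section 8.2: p₁ = 0.75, p₂ = 0.75 + 0.16 = 0.91, α = 0.025, power 0.80, losses 5%, 75 per arm. From section 8.1: chi-square test, threshold 0.025, all randomised. Sidedness is not stated, so both readings are shown. Critical values are 1.960 (one-sided) and 2.241 (two-sided), and z for 80% power is 0.8416.

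**Step 1: try to reproduce 75 per arm.**

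n = [z_α √(2p̄q̄) + z_β √(p₁q₁ + p₂q₂)]² / d², where p̄ = 0.83, √(2 × 0.83 × 0.17) = 0.5312, √(0.1875 + 0.0819) = 0.5190 and d = 0.16.

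- One-sided: (1.960 × 0.5312 + 0.8416 × 0.5190)² / 0.0256 = 85.3, so 86 per arm. With 5% losses, 86 / 0.95 = 90.5, so 91 (273 in total).
- Two-sided: (2.241 × 0.5312 + 0.8416 × 0.5190)² / 0.0256 = 103.5, so 104 per arm. With 5% losses, 104 / 0.95 = 109.5, so 110 (330 in total).

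Unpooled-variance and arcsine forms give 87 to 88 (one-sided) or 106 to 107 (two-sided) with losses, and a continuity correction gives more. The nearest standard variant uses one-sided α = 0.05, which is not the stated level, and gives 72. The figure of 75 is not reproduced.

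**Step 2: dilute the rates.** If 0.75 and 0.91 apply only to those retained, and 5% in each arm are lost and scored as non-completers:

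- control: 0.95 × 0.75 = 0.7125
- experimental: 0.95 × 0.91 = 0.8645
- difference: 0.152

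The same formula then needs 113 per arm (one-sided) or 136 (two-sided). The ratios to step 1 are 113 / 86 = 1.31 and 136 / 104 = 1.31. A 5% loss allowance multiplies the sample by only 1 / 0.95 = 1.05.

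**Step 3: power at 75 per arm.** Exact power is the sum of the binomial probabilities of all pairs of counts for which the uncorrected chi-square test (or its one-sided equivalent) is significant.

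| Handling of losses | Per arm | Rates | Two-sided | One-sided |
|---|---|---|---|---|
| Rates already include losses | 75 | 0.75 / 0.91 | 65.6% | 76.5% |
| 5% losses excluded | 71 | 0.75 / 0.91 | 62.3% | 73.9% |
| 5% losses added as non-completers | 75 | 0.7125 / 0.8645 | 52.2% | 63.5% |

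The normal approximation gives slightly lower figures in the first and third rows: 64.6% (74.7%) and 51.5% (62.7%).

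**Step 4: split the shortfall from 80%.**

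- Rates already include losses: the whole gap, 80 − 65.6 = 14.4 points two-sided or 80 − 76.5 = 3.5 one-sided, comes from 75 per arm not following from the inputs.
- Losses come on top: a further 65.6 − 52.2 = 13.4 points two-sided, or 76.5 − 63.5 = 13.0 one-sided. The sample size then accounts for about half of the two-sided shortfall and a minority of the one-sided one.

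**Step 5: can the denominator move the decision?** Illustrative counts, two-sided chi-square p against 0.025:

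- 4 lost per arm, 54 vs 65 completers: p = 0.027 over 75 per arm, 0.012 over 71. The decision changes.
- 4 lost per arm, 53 vs 65 completers: p = 0.017 and 0.007. It does not.
- 2 lost on control and 6 on experimental, 55 vs 63 completers: p = 0.111 over all randomised, 0.011 with losses excluded. It changes, but this split is assumed.

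**The case against.** The best defence is that the analysis set is not in doubt. Section 8.1 says all randomised, the one-dose restriction is kept for safety, and no text removes anyone from the efficacy denominator. That stands: the definition governs and *modified* is a wrong label.

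A reader might go further and infer that section 8.2 takes lost participants out of the denominator and so contradicts section 8.1. The documents do not support that. Section 8.2 states no denominator, and because 75 per arm cannot be reproduced, nobody can see how the 5% was used. The allowance is unexplained, not proof of a second analysis set.

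It can also be said that scoring is largely settled already, since a participant without the required doses in the window fails section 3.1, and that finer rules belong in an analysis plan. This is fair, and a missing scoring rule or sensitivity analysis would not be a finding alone. The stated power, however, is a protocol figure that can be checked here.

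Finally, 0.75 comes from the sponsor's own experience and may already count losses. If so, the drop to 52% (64%) disappears and the 5% is surplus. Power is still 65.6% (76.5%), below 80%.

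**Conclusion.** The point holds as a mismatch of label, loss allowance and stated power. On the all-randomised set, 75 per arm gives about 66% power per comparison two-sided (76.5% one-sided) if the assumed rates include losses, and about 52% (64%) if 5% losses in each arm are added as failures. The stated figure is 80%. The first gap comes from a sample size that does not follow from its inputs. Loss handling contributes nothing to about 13 points, depending on what 0.75 means.

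These figures assume an uncorrected chi-square test, the 0.16 difference as stated, and equal losses in the arms where losses are added.

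A reader might also infer that the choice of denominator changes the primary result. It can, in borderline data or with unequal losses, but need not. Equal 5% losses move the difference only from 0.16 to 0.152, and the protocol gives no loss split by arm.

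**What to change.** In section 8.1, delete *modified*. State that all randomised participants are analysed in their assigned arm, and that anyone without documented completion counts as a non-completer, including those lost, withdrawn or never treated.

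In section 8.2, keep the total at 225 and make three statements:

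- that 0.75 and 0.91 are completion rates among all randomised, with losses counted as non-completion (if the source of 0.75 left losses out, lower the rates accordingly);
- whether α = 0.025 is one- or two-sided;
- the power actually delivered at 75 per arm on that basis.

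The 5% allowance then has no separate role and should not be presented as protecting power.

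This takes a few sentences and no new data. The cost is a clearly less favourable stated power: about 66% or 76.5% in place of 80%, or less if losses come on top.

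### Repeating the primary comparison within each dialysis subgroup cannot show whether the treatment effect differs by modality; an interaction test with descriptive subgroup estimates would

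*Protocol*

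**What the plan says.** Protocol section 8.1 compares the completion proportion in 3HR with that in 3HP and with that in 4R. It then motivates the subgroups: "Since renal replacement therapy could have a potential influence on medication tolerance, especially INH, and thus could influence outcome". The method follows in the same sentence: "the analysis for the primary endpoint will be performed for the population as a whole and by subgroups". The three subgroups are the renal-therapy strata used for randomisation in section 3.3.

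For binary outcomes the differences are tested "or by chi-square analysis for categorical variables". One threshold is given for the whole section: "Statistical significance was set at a p-value <0.025". No exception is made for subgroups, and neither sidedness nor continuity correction is stated. The section does not label the subgroup analyses exploratory, and it does not call them confirmatory. It promises 95% confidence intervals where possible.

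Section 8.2 sizes the trial for the overall comparisons only: "With an α= 0.025, β= 0.20, and 5% expected losses", "assuming a 0.75 proportion of treatment completion in the control arm (3HR", a 0.16 increase, and 75 per arm.

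**The concern.** The stated reason concerns effect modification. Isoniazid is singled out, and it is in 3HR and 3HP but not in 4R, so the natural question is whether the contrast between arms changes with modality. The stated method asks something else, namely whether each contrast is significant inside each modality taken alone. No step compares the effects between modalities.

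A subgroup p-value depends on the number of patients as well as on the effect. A large subgroup can be significant and a small one not while the true effect is the same in both. The likely harm is a report that a regimen improves completion in haemodialysis but not in peritoneal dialysis, when the data show only that one group was bigger or luckier. Two comparisons in three subgroups also make six further tests, and 0.025 is the only threshold in the text.

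**Working it through.** The protocol states no subgroup power, subgroup size or subgroup error rate, so there is no figure of its own to reproduce on this point.

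**Inputs from the protocol.** Completion 0.75 in control and 0.75 + 0.16 = 0.91 in an experimental arm; 75 per arm (section 8.2). Chi-square, p<0.025, two comparisons sharing the 3HR control, three subgroups (section 8.1).

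**Assumptions.** Per-arm subgroup sizes of 25/25/25, 30/35/10 or 22/45/8 (non-dialysis/haemodialysis/peritoneal dialysis). The p-value is two-sided, so chi-square on 1 df must exceed 5.024. Results are given without and with Yates correction, which is the default for a 2×2 table in R's chisq.test; the protocol names R.

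**Step 1. Power in one subgroup, 0.75 versus 0.91.** Exact, summing the two binomial distributions over all tables with p<0.025:

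| n per arm | uncorrected | Yates |
|---|---|---|
| 8 | 0.056 | 0.002 |
| 10 | 0.039 | 0.009 |
| 22 | 0.194 | 0.092 |
| 25 | 0.235 | 0.099 |
| 30 | 0.284 | 0.160 |
| 35 | 0.339 | 0.191 |
| 45 | 0.423 | 0.310 |

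**Step 2. Mixed verdicts when the effect is the same everywhere.** For one comparison the three subgroups contain different patients, so the tests are independent. With powers p1, p2, p3:

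P(mixed) = 1 − p1·p2·p3 − (1−p1)(1−p2)(1−p3)

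- 25/25/25, uncorrected: 1 − 0.235³ − 0.765³ = 1 − 0.013 − 0.448 = 0.54
- 30/35/10, uncorrected: 1 − 0.004 − (0.716 × 0.661 × 0.961 = 0.455) = 0.54
- 22/45/8, uncorrected: 1 − 0.005 − (0.806 × 0.577 × 0.944 = 0.439) = 0.56
- With Yates, in the same order: 0.27, 0.33 and 0.38

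All three subgroups are significant together in about 1% of trials or fewer. A true uniform effect would therefore almost never look uniform.

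**Step 3. False positives when no arm differs (0.75 in all arms).** If the six tests were independent, the chance of at least one p<0.025 would be 1 − 0.975⁶ = 0.141. The two tests in a subgroup share a control, so each pair is enumerated jointly and the three subgroups are then multiplied:

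| split | uncorrected | Yates |
|---|---|---|
| 25/25/25 | 14.4% | 4.9% |
| 30/35/10 | 12.4% | 4.7% |
| 22/45/8 | 13.5% | 4.5% |

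These are totals across six tests, counting significance in either direction.

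**Step 4. Increment over the two overall tests.** By simulation, uncorrected, at least one of the two overall tests is significant in about 4.7% of trials. At least one of all eight is significant in 16.4%, 14.4% and 15.3% for the three splits. The differences are 11.6, 9.8 and 10.6 points, so about 10-12.

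**Step 5. Sensitivity of step 3.** At 0.88 completion in all arms the total is 9-12% uncorrected and 1.5-2.1% with Yates. Counting only results that favour an experimental arm at two-sided 0.025, the large-sample figure is 6.8%.

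**The case against.** The strongest reply is that this belongs in the statistical analysis plan, which is not shown. Whether there is an interaction test and what status the subgroups have are often settled there, and their absence from a protocol is not an error. That is right about absence. Here, however, the protocol names a method and a reason for it, and the two do not match. A later plan could add an interaction test, but the protocol text would still present the repeated comparison as the way to examine modality.

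Several other parts of the reply stand:

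- A reader might infer that the protocol sets 0.025 as the criterion for subgroup claims, or treats the subgroups as confirmatory. It does neither. The threshold is a general sentence later in the section, and its use in subgroups is an inference. The objective, endpoint and sample size concern the overall comparisons only.
- A reader might infer that the subgroup tests add 12-14 points of false-positive risk. They do not: that is the total for the six tests in the uncorrected, either-direction case, and the increment is about 10-12 points. With Yates correction the total is about 5%.
- Subgroup sizes are assumed. If one modality dominates, its power is not negligible (about 42% at 45 per arm, uncorrected). Low subgroup power is no fault in a trial not sized for subgroups.
- The promised 95% confidence intervals already supply part of the remedy.
- An ordinary logistic interaction model can be unstable when a subgroup has about 10 patients per arm and completion near 91%, because cells may be empty.

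None of this rescues separate p-values as evidence that effects differ.

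**Conclusion.** The point holds as a mismatch between purpose and method. Its firmest support is the mixed-pattern result, which uses the protocol's own effect size: with no true difference between modalities, an apparent difference in significance arises in about 54-56% of trials uncorrected and 27-38% with Yates. It is frequent under all three assumed splits and under either version of the test.

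The false-positive figure is secondary and more fragile. The 12-14% total requires uncorrected chi-square, both directions counted, 0.75 completion in all arms and the assumed sizes; it falls to about 5% with Yates. It does not show that the trial's primary error rate is inflated, because the protocol does not say that a subgroup result can support a superiority claim. The overall comparisons are not affected, so this is a cheap improvement and not a flaw in the main result.

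**What to change.** In section 8.1, replace the repeated subgroup analysis with three statements:

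1. Whether the effect on completion differs by modality is assessed by an arm-by-modality interaction test, with the model and effect scale named. If a subgroup proves small, use a method suited to sparse cells, for example penalised logistic regression.
2. Completion proportions and risk differences against 3HR are shown for each modality with confidence intervals, as descriptive results.
3. No efficacy claim rests on a subgroup p-value.

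The section should add that the interaction test will have low power, so its non-significance is not proof of equal effects; the intervals should carry the interpretation.

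The cost is a few sentences and one model. Modality is already a randomisation stratum, so no new data, visits or patients are needed.
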